### Statistical analysis

The statistical analysis plan will be developed and performed by independent statisticians from the data monitoring committee. SAS software V.9.4 (SAS Institute, Cary, NC) will be used for the statistical analysis. Based on the intention-to-treat principle, the full analysis set and per protocol set will be adopted as the primary analysis populations. A two-sided *p* < 0.05 will indicate significance in all statistical tests. Appropriate descriptive indicators and hypothesis testing methods will be selected cautiously. Data, including demographics, baseline characteristics, and safety, will be summarized by treatment arm.

The primary efficiency outcomes are powered by a superiority test to detect the change in 24-h SBP from baseline to 6 months after the intervention. The sensitivity analysis will have a stratifying variable center as a fixed effect of an analysis of covariance (ANCOVA). A BP reduction will be tested by paired *t*-tests with 95% confidence intervals for the differences between treatment arms. Other categorical data will be tested using either Pearson’s χ^2^ test or Fisher’s exact test. Rank data will be tested by either the Wilcoxon rank sum test or the Cochran–Mantel–Haenszel test. Mixed-model repeated measures analysis including terms for the baseline measurement, types of drugs taken, and medication adjustments during the follow-up will be used for the reduction in BP.

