### Randomization

A total of 200 enrolled patients will be scheduled for renal angiograms to confirm the anatomical suitability of their renal arteries. A stratified block randomization of patients to receive cryo-RDN or the sham procedure will be performed at a ratio of 1:1 according to study site. To minimize the human factors, the allocation will remain concealed until the patients are anesthetized in the interventional lab. In addition, patients allocated to the sham group will be anesthetized for 30 min in the same manner as those undergoing cryo-RDN.

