### Sample size calculation

PASS 13 was used to estimate the sample size. This trial was designed to compare the difference in 24-h SBP as a change from baseline to 6 months between the cryo-RDN treatment arm and the sham treatment arm. Based on data from previous studies, we chose a sample size of 81 per treatment arm. The between-group comparison will be powered at 95% to establish the superiority of cryo-RDN for the primary endpoint at a single-sided significance level of 0.025, considering a true 24-h SBP difference as 8 mmHg with a common standard deviation of 18 mmHg. Given an estimated dropout rate of approximately 20%, we increased the sample size to 100 per arm for a total of 200 participants.

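### The centre-adjusted ANCOVA is only a sensitivity analysis and the primary test appears to be unadjusted, so available precision is given up

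*Protocol article*

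**What the plan says.** The Randomization section describes stratified blocks and says that allocation "will be performed at a ratio of 1:1 according to study site". There are 13 centres (Study patients). The Study visits section has 24-h ambulatory blood pressure measured at baseline and at every later visit. The primary outcome is the between-arm difference in the change in 24-h SBP from baseline to 6 months.

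The Sample size calculation section sizes this comparison "considering a true 24-h SBP difference as 8 mmHg with a common standard deviation of 18 mmHg", "at a single-sided significance level of 0.025". It mentions no covariate and no correlation between baseline and follow-up.

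The Statistical analysis section describes four procedures that could bear on the primary endpoint:

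- a superiority test for the change in 24-h SBP, with no model or covariates named;
- an ANCOVA: "The sensitivity analysis will have a stratifying variable center as a fixed effect of an analysis of covariance (ANCOVA");
- paired t-tests for blood pressure reduction, mentioned together with confidence intervals for differences between arms;
- a mixed model for repeated measures with terms for the baseline measurement, the types of drugs taken and medication adjustments during follow-up. It has no stated rank and no listed centre term.

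**The concern.** A factor used to stratify the randomisation would normally be in the primary model. Stratifying by site removes between-centre variation from the treatment contrast. A test that leaves centre out still counts that variation in its standard error, which is then too large whenever centres differ. Baseline 24-h SBP is also measured on everyone, and conditioning on it removes whatever part of the change it predicts.

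As written, centre is assigned to a supporting analysis. Baseline is listed only in a model that also contains medication adjustments made after randomisation. The Interventions section ties those adjustments to post-procedure symptoms and blood pressure, so treatment can influence them. A contrast conditioned on them is not a clean estimate of the treatment effect, and that model is a poor substitute for a baseline-adjusted primary analysis. No described model is both stated to be primary and adjusted for centre and baseline without post-randomisation terms.

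What is at stake is power in a trial that has less of it than the article states.

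**Working it through.** **Inputs from the article.** Difference 8 mmHg; SD 18 mmHg, taken as the SD of the change (the text does not say so outright); 81 evaluable per arm; one-sided 0.025. The two-sided 0.05 rule that "will indicate significance in all statistical tests" is the same threshold in the direction of benefit. There are 13 centres.

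**Assumptions, not in the article.** Baseline SD s0, correlation ρ between baseline and 6 months, and the share of the change variance lying between centres (ICC).

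**1. The plan's own figure.** n per arm = 2(z₀.₉₇₅ + z_power)² × 18²/8².
- 95% power: 2 × (1.960 + 1.645)² × 5.0625 gives 132 (133 with the t distribution).
- 80% power: 2 × (1.960 + 0.842)² × 5.0625 gives 80 (81 with the t distribution).

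The stated 81 is therefore the unadjusted two-sample t-test size for 80% power. Its actual power is 80.3%. This supports reading the primary test as an unadjusted comparison of change scores.

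**2. Adding baseline.** With change variance 18² = 324:
- s1 = ρ·s0 + √(324 − s0²(1 − ρ²)), the 6-month SD implied by s0 and ρ;
- residual variance = s1²(1 − ρ²), which equals 324 − (1 − b)²·s0² with slope b = ρ·s1/s0.

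The second form shows that adjustment cannot raise the residual variance, and that the gain vanishes when b = 1.

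For the range of s0: patients on two or three drugs must have a 24-h SBP from 140 to below 170 mmHg at the second screening visit, and that visit supplies the baseline. In a 30 mmHg window a uniform spread has SD 30/√12 = 8.7, and no spread can exceed 15.

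Power at 81 per arm (noncentral t, one degree of freedom for baseline):

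| s0 | ρ = 0.3 | ρ = 0.5 | ρ = 0.7 |
|---|---|---|---|
| 8.7 | 81% | 81% | 87% |
| 12 | 86% | 81% | 83% |
| 15 | 93% | 83% | 81% |

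Two cells in full:
- s0 = 15, ρ = 0.3: s1 = 4.5 + √(324 − 204.75) = 15.42; residual variance 237.8 × 0.91 = 216.4; SD 14.7; power 93%.
- s0 = 8.7, ρ = 0.5: s1 = 4.35 + √(324 − 56.77) = 20.70; residual variance 428.4 × 0.75 = 321.3; SD 17.9; power 80.6%.

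Between the tabulated points the gain can fall to nil. At s0 = 10 and ρ = 0.5, b = 1.04 and power stays at 80.3%.

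**3. Adding centre only.** Residual SD = 18√(1 − ICC), with 12 degrees of freedom lost:
- ICC 0: 80.2%
- ICC 0.05: 82.2%
- ICC 0.10: 84.2%

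Against 80.3% that is about 0 to 4 points. Part of it comes from the stratified design itself: by the normal approximation the unadjusted test's own power rises from 80.7% at ICC 0 to 82.0% at ICC 0.10.

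**4. Direction of the error when centre is omitted.** True one-sided level = 1 − Φ(1.960/√(1 − ICC)):
- ICC 0.05: 1.960/0.975 = 2.011, level 0.022
- ICC 0.10: 1.960/0.949 = 2.066, level 0.019

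Both are below 0.025, so the unadjusted test is slightly conservative.

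**The case against.** The primary model is never named. Sizing by a two-sample formula does not commit a trial to an unadjusted analysis; many trials are sized that way and analysed with covariates. Covariate lists are commonly left to the statistical analysis plan, which the article says is still to be developed. The adjusted ANCOVA is already planned, and randomisation keeps unadjusted change scores unbiased. Much of this stands: the unadjusted primary test is an inference, and the issue is efficiency. It does not dispose of the point, because the article itself gives the centre-adjusted model its supporting role. That is a stated choice, not an omission.

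A reader might infer a much larger and firmer gain. If baseline and 6-month variances are equal, ANCOVA variance is (1 + ρ)/2 of the change-score variance, and power becomes 94%, 90% and 86% at ρ of 0.3, 0.5 and 0.7. The arithmetic is right, but a change SD of 18 then implies a baseline SD of 18/√(2(1 − ρ)) = 15.2, 18.0 and 23.2 mmHg. The 30 mmHg window for patients on two or three drugs cannot produce any of these. The criteria for patients on four or five drugs set no upper limit on 24-h SBP, so the whole-trial SD could be larger, but the article does not give their share.

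A reader might also infer that the result would be biased or the type I error inflated. Step 4 of the working shows the opposite direction for the omitted stratifier.

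**Conclusion.** The point holds as one of efficiency. Centre is assigned to a sensitivity analysis, the primary test appears to be unadjusted, and the only model listing baseline has no role and carries a post-randomisation term. With 81 per arm and a change SD of 18 mmHg, baseline adjustment would move power from about 80% to somewhere between about 81% and 93% over the tabulated assumptions, and to no gain at all where the slope of follow-up on baseline is 1. Centre would add about 0 to 4 points. Baseline SD, correlation and ICC are all assumed, so the direction is secure and the size is not.

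Adjustment should not be read as closing the gap in the sample size section. The statement "The between-group comparison will be powered at 95% to establish the superiority of cryo-RDN" and the statement "we chose a sample size of 81 per treatment arm" do not agree: 81 per arm gives about 80% on the stated inputs. That is a separate error, to be corrected in its own right.

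**What to change.** Name a single primary analysis: an ANCOVA of the 6-month change in 24-h SBP (or the 6-month contrast of a mixed model) with treatment, baseline 24-h SBP and centre, and no post-randomisation terms. With 200 patients over 13 centres, about 15 each on average, fix a rule for pooling small centres before unblinding. Make the unadjusted comparison of change scores and the mixed model with medication adjustments supportive, and state the role of each.

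The cost is a text edit plus 12 degrees of freedom for centre and 1 for baseline, about 13 out of 2 × 81 − 2 = 160. If centre explained nothing, its 12 degrees of freedom would cost about 0.1 point of power or less. No extra patients or measurements are needed.

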## Methods/design

### Study design

Our trial is a prospective multicentered single-blinded randomized sham-controlled trial to evaluate the efficiency in BP reduction and safety in Chinese patients with uncontrolled hypertension compared with the sham arm. It uses a Cryofocus RDN device. The study will be conducted in accordance with the principles of the Declaration of Helsinki in 13 medical centers nationwide. Each patient will be screened twice before receiving the cryo-RDN, if applicable. A brief flow chart (Fig. 2) is listed below.

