### Outcome measures

The primary outcome of this study is the difference in the change in 24-h SBP from baseline to 6 months between the cryo-RDN treatment arm and the sham treatment arm. At each participating site, one or two staff members from the laboratory department, and not the clinical department, will be allocated to undertake the 24-h BP measurements during the study period.

The secondary outcomes are as follows:
Difference in change in 24-h SBP (daytime and nighttime) from baseline to 6 months between the cryo-RDN treatment arm and the sham treatment armDifference in change in 24-h SBP (daytime, nighttime, and 24-h) from baseline to 6 months between the cryo-RDN treatment arm and the sham treatment armDifference in change in office BP (SBP and DBP) from baseline to 6 months between the cryo-RDN treatment arm and the sham treatment armCharacteristics of patients who required an adjustment to their medication after the interventionAdherence of patients to taking their antihypertensive drug based on the eight-item Morisky Medication Adherence ScaleOperational performance evaluation of the test device in the cryo-RDN treatment armSide effects possibly caused by the test deviceMajor adverse eventsOther adverse events

Safety endpoints primarily include any adverse incidents, including but not limited to puncture-related vascular injury, renal artery complications, renal complications, systematic reactions and a change in renal function, which may be caused by the test device or other factors.

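### The analysis section attaches a paired t-test to the between-arm difference in BP reduction, although the two randomised arms are independent

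*Protocol article*

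**What the plan says.** The Statistical analysis section of the protocol article gives this rule for blood pressure: "A BP reduction will be tested by paired *t*-tests with 95% confidence intervals for the differences between treatment arms".

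The rest of the article describes two unmatched groups compared with each other:

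- Study design: a "prospective multicentered single-blinded randomized sham-controlled trial".
- Randomization: "A stratified block randomization of patients to receive cryo-RDN or the sham procedure will be performed at a ratio of 1:1 according to study site". Each patient has one procedure, and no matching across arms is described.
- Outcome measures: the primary outcome is "the difference in the change in 24-h SBP from baseline to 6 months between the cryo-RDN treatment arm and the sham treatment arm".
- Sample size calculation: "The between-group comparison will be powered at 95" per cent, for a true difference of 8 mmHg with a common SD of 18 mmHg, "at a single-sided significance level of 0.025", with 81 patients per arm before dropout.

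The Statistical analysis section names three other things that bear on the point. The primary outcome gets a superiority test of unspecified form. An ANCOVA with centre as a fixed effect is labelled a sensitivity analysis. A mixed model for repeated measures is to be used for the reduction in BP; its listed terms are baseline, types of drugs and medication adjustments during follow-up.

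**The concern.** A paired t-test needs two measurements that belong together. Within one patient, baseline and 6 months form such a pair. A cryo-RDN patient and a sham patient do not. The sentence joins a within-patient test to a between-arm contrast, so it can be carried out in only two ways, and neither fits the trial.

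In the first, patients are paired across arms by some rule that the article does not give. In the second, change from baseline is tested separately in each arm. The second is the more serious, because a within-arm fall contains everything that lowers the reading over six months: regression to the mean in patients selected for raised BP, response to a sham procedure under anaesthesia, and the standardised drugs. The sham arm is there so that these can be subtracted, and a within-arm test does not subtract them.

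**Working it through.** **1. Which comparison the design calls for.** The sample size inputs (Sample size calculation section) are a difference of 8 mmHg, SD 18 mmHg, one-sided alpha 0.025 and 81 per arm. For an independent two-sample t-test:

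- standard error = 18 × √(2/81) = 2.83 mmHg
- noncentrality = 8 / 2.83 = 2.83
- critical t on 2 × 81 − 2 = 160 df = 1.975
- power from the noncentral t = 80.3%

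The smallest n per arm that gives 80% power is 81; for 95% power it is 133. The stated 95% is therefore not reproduced, which is a separate matter. What counts here is that 81 is exactly the unpaired two-sample size at 80% power. A paired calculation with SD 18 for the paired difference needs 42 pairs for 80% power and 68 for 95%, so it does not give 81 at either level. The figures point to an unpaired comparison.

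**2. Reading A: patients paired across arms.** No pairing rule is given. If pairs were formed without regard to outcome, the standard error would stay at 2.83 mmHg and only the degrees of freedom would fall, from 160 to 80. The critical t becomes 1.990 and power 79.8%, against 80.3% unpaired. The type I error rate stays at its nominal level. The defects are that the pairs are undefined, that the result depends on which pairing is chosen, and that patients without a partner are lost when arm sizes differ, which is likely with about 20% dropout.

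**3. Reading B: change tested within each arm.** This illustration rests on three assumptions that the article does not state:

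- efficacy is claimed when cryo-RDN is significant and sham is not;
- the 18 mmHg is the SD of the change;
- both arms fall by the same amount, so there is no device effect.

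With 81 per arm and two-sided 0.05 (the article's rule: "A two-sided *p* < 0.05 will indicate significance in all statistical tests"), the standard error within an arm is 18/√81 = 2.0 mmHg. The noncentrality is fall / 2.0 on 80 df. If p is the chance that one arm is significant, the pattern occurs with probability p × (1 − p), as the arms are independent.

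| Equal fall in both arms (mmHg) | Noncentrality | p | p × (1 − p) |
|---|---|---|---|
| 2 | 1.0 | 0.17 | 0.14 |
| 3 | 1.5 | 0.32 | 0.22 |
| 4 | 2.0 | 0.51 | 0.25 |
| 5 | 2.5 | 0.70 | 0.21 |
| 6 | 3.0 | 0.84 | 0.13 |
| 8 | 4.0 | 0.977 | 0.023 |

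The nominal rate for a wrong claim in favour of the device is 2.5%. The pattern is most frequent at a common fall near 4 mmHg. It returns to about nominal at 8 mmHg, because by then both arms are nearly always significant.

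**The case against.** The strongest reply is that this is one misplaced word in a condensed article. The sentence concerns BP reduction in general and comes after the primary outcome and its sensitivity analysis. It may mean paired tests for change within each arm and, separately, confidence intervals for the difference between arms; the between-arm estimate would then still be reported. The sample size is plainly two-sample, and the ANCOVA and the mixed model offer further routes to a comparison of the arms.

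Much of this stands. A reader might infer that the paired t-test is the primary analysis, or that the plan contains no valid between-arm test. The article supports neither: it does not label this test primary, it gives the primary outcome a superiority test, and the exact form of that test may properly be left to the analysis plan. A reader might also take 25% as the trial's false-positive rate. It is not, since no section says that efficacy will be judged arm by arm, and the figure depends on an assumed common fall. Nor does pairing across arms inflate error, provided the pairs are fixed without regard to outcome.

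What does not stand is that the other methods put the sentence right. The ANCOVA is labelled a sensitivity analysis. The mixed model is not labelled primary, and treatment arm is not among its listed terms. Leaving detail to an analysis plan covers what an article omits, not a test that it names and ties to the wrong contrast.

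**Conclusion.** The concern holds in a limited form. The sentence names a paired test for a contrast between independent arms, which conflicts with the article's own allocation, primary outcome and sample size. That conclusion follows from the text and needs no assumption.

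The size of the harm depends on how the sentence would be carried out. With outcome-blind pairing across arms, the loss is about half a percentage point of power at 81 pairs, plus any patients left unpaired. With arm-by-arm testing used as evidence of efficacy, the wrong pattern would appear in about 13 to 25% of null trials for a common fall of 2 to 6 mmHg and about 2% at 8 mmHg, given SD 18 and 81 per arm. Because that decision rule is not in the article and other between-arm methods are named, this is a point that should be fixed rather than one that invalidates the plan.

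**What to change.** Replace the sentence with a between-arm comparison of the 6-month change in 24-h SBP, reported with its 95% CI. The minimum is an independent two-sample t-test, which is what 81 per arm corresponds to. An ANCOVA with baseline 24-h SBP and centre is also available, since both variables are already collected; choosing it over the t-test is a preference, not a requirement. State that paired changes within each arm are descriptive and carry no claim of efficacy.

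The cost is one sentence, with no new data and no change to visits. The article says that recruitment had not begun at submission. The change should be made, and carried into the analysis plan, before any unblinding.

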### Interventions

Eligible patients will undergo either cryo-RDN with Cryofocus system or dual renal angiography only. It is expected that their previously prescribed standardized antihypertensive drugs will remain unchanged in the 6-month follow-up period after the intervention.

However, if in the first 3 months after the intervention a patient experiences dizziness, fatigue, or other symptoms of hypotension, or after 4–6 months the patient has office SBP < 100 mmHg and office DBP<50 mmHg, then the investigators can decrease the number or the dosage of the antihypertensive drugs. Moreover, additional drugs can be added at 4–6 months if a patient taking two or three types of standard antihypertensive drugs has office BP>160/110 mmHg or if a patient taking four types of standard antihypertensive drugs has office BP > 180/110 mmHg (the rules for adjusting dosages are listed in Additional file 2: Table S2).

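### The mixed model for BP reduction adjusts for drug changes made after randomisation in response to follow-up BP or symptoms, so it does not estimate the randomised treatment effect

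*Protocol article*

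**What the plan says.** The Statistical analysis section describes a "Mixed-model repeated measures analysis including terms for the baseline measurement, types of drugs taken, and medication adjustments during the follow-up", which "will be used for the reduction in BP". It does not say which BP measure is modelled or where the model ranks beside the superiority test, the ANCOVA sensitivity analysis with centre and the t-tests named in the same section. The section also invokes the intention-to-treat principle.

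The Interventions section sets out when medication may change. The starting position is stability: "It is expected that their previously prescribed standardized antihypertensive drugs will remain unchanged in the 6-month follow-up period after the intervention". The exceptions are:

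- Drugs may be added for high office BP. The rule for the smaller regimens reads "additional drugs can be added at 4–6 months if a patient taking two or three types of standard antihypertensive drugs has office BP>160/110 mmHg". For the next larger regimen the systolic threshold is higher, and the rule applies "if a patient taking four types of standard antihypertensive drugs has office BP > 180/110 mmHg".
- Drugs may be reduced in the first 3 months if "a patient experiences dizziness, fatigue, or other symptoms of hypotension", or later if "after 4–6 months the patient has office SBP < 100 mmHg and office DBP<50 mmHg".

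Outcome measures defines the primary outcome as the between-arm difference in 24-h SBP change to 6 months. It lists office BP change, and the characteristics of patients whose medication was adjusted, as secondary outcomes.

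**The concern.** A covariate measured before randomisation can be adjusted for without changing what the comparison means. A drug change made in months 1 to 6 is different. It follows from BP after the procedure, which the device is meant to lower. If cryo-RDN works, fewer cryo-RDN patients cross the add-on threshold. Those in either arm who do cross it are mostly those whose BP stayed high. Holding the drug change fixed therefore compares selected subsets of the two arms and removes part of the effect under test.

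The coefficient could be reported as the treatment effect on BP although it is neither of two interpretable quantities: the effect of allocation whatever happens to medication, or the effect had medication stayed unchanged.

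**Working it through.** **What the documents settle.** Side by side, the two sections show that the covariate arises after randomisation and depends on follow-up BP or symptoms. That is enough to show that the coefficient is not the contrast defined under Outcome measures. Only the size needs calculation, and the article gives no figure for it.

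**Inputs from the article.** Device effect 8 mmHg and SD of 24-h SBP change 18 mmHg (Sample size calculation); 1:1 allocation (Randomization); add-on threshold 160 mmHg systolic for patients on two or three drugs (Interventions).

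**Assumptions not in the article.**
- Baseline 24-h SBP is normal, mean 150, SD 9, limited to 135–170. Baseline office SBP is that value plus a normal term, mean 13, SD 7, limited to 150–180.
- Mean sham change is −4 mmHg (24-h) and −8 mmHg (office). The device adds −8 to both. Office change also has SD 18.
- The correlation between office and 24-h changes is 0.3, 0.5 or 0.7.
- A drug is added whenever follow-up office SBP exceeds 160 or, as a rarer trigger, 175. It lowers 24-h SBP by 0 or 8 mmHg.

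**Method.** 400,000 simulated patients per scenario. Six-month 24-h SBP change is regressed on arm and baseline, with and without an indicator for an added drug. This is a single-timepoint simplification of the mixed model. Estimates are reductions in mmHg.

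| Correlation | Drug effect | Trigger | Added, cryo / sham | Without term | With term | Loss |
|---|---|---|---|---|---|---|
| 0.3 | 0 | 160 | 0.27 / 0.41 | 7.94 | 6.73 | 1.21 |
| 0.3 | 0 | 175 | 0.09 / 0.17 | 8.03 | 7.26 | 0.77 |
| 0.3 | 8 | 160 | 0.27 / 0.41 | 6.83 | 6.76 | 0.07 |
| 0.3 | 8 | 175 | 0.09 / 0.17 | 7.36 | 7.27 | 0.09 |
| 0.5 | 0 | 160 | 0.27 / 0.41 | 8.06 | 6.06 | 2.00 |
| 0.5 | 0 | 175 | 0.09 / 0.17 | 7.99 | 6.73 | 1.26 |
| 0.5 | 8 | 160 | 0.27 / 0.41 | 6.86 | 5.99 | 0.87 |
| 0.5 | 8 | 175 | 0.09 / 0.17 | 7.43 | 6.82 | 0.61 |
| 0.7 | 0 | 160 | 0.27 / 0.41 | 8.05 | 5.28 | 2.77 |
| 0.7 | 0 | 175 | 0.09 / 0.17 | 8.01 | 6.25 | 1.76 |
| 0.7 | 8 | 160 | 0.27 / 0.41 | 6.92 | 5.26 | 1.66 |
| 0.7 | 8 | 175 | 0.09 / 0.17 | 7.34 | 6.23 | 1.11 |

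**Why the term misleads.** On the change scale, least squares gives, to close approximation,

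estimate without term = estimate with term + γ × (share with added drug in cryo − share in sham),

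where γ is the fitted coefficient of the added-drug term. For correlation 0.7, drug effect 8 and trigger 160: −6.92 = −5.26 + γ × (0.27 − 0.41), so γ = 1.66 / 0.14 ≈ +11.9 mmHg. The drug was built to lower BP by 8, yet its coefficient is positive: the term records who failed to respond.

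**The effect at unchanged medication is missed too.** It is 8 mmHg by construction. The adjusted estimates run from 5.26 to 7.27, a shortfall of 8 − 7.27 = 0.73 to 8 − 5.26 = 2.74.

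**The near-zero losses are a cancellation.** At correlation 0.3 and trigger 160, the non-response part of γ is 1.21 / 0.14 ≈ 8.6 mmHg (the row with no drug effect), which an 8 mmHg drug effect nearly offsets. A larger drug effect would put the adjusted estimate above the unadjusted one, but still short of 8.

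**No true effect.** With equal management the shares are equal (0.41 / 0.41 or 0.17 / 0.17), the last part of the identity vanishes, and every estimate lay within 0.14 mmHg of zero with or without the term. If drugs were added less readily in one arm, the shares would differ and the term would shift the estimate in a direction set by which arm that was.

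**The case against.** **The model may be only supportive.** A reader might infer that the primary test is biased. The article does not support that: it ties the primary outcome to a superiority test and mentions the mixed model last, without endpoint or rank. This stands and limits the severity.

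**The trigger is not the primary outcome.** A reader might also infer that drug changes are driven by the primary endpoint itself. They are driven by office BP, or early on by symptoms. For 24-h SBP the trigger is a correlated measure. This also stands, and is why the correlation is varied.

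**A loss near the top of the range is not established.** The simulation simplifies the rules in Interventions. Patients on four drugs have a higher threshold, no add-on trigger is stated for five, a diastolic component exists, and additions are permitted rather than required. Variants closer to those rules were run from a separate set-up that lost about 2.3 mmHg with an 8 mmHg drug effect. With 40% of patients assumed on four drugs and 10% on five, the loss was 1.3 mmHg. Further steps (both BP components required, weaker correlation, half of eligible patients given a drug) brought it to 0.3–0.4. This stands against any single figure.

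**Study visits fall at 1, 3 and 6 months, so a drug added at month 6 could hardly affect that day's reading.** True, but this does not rescue the term. Such a patient resembles the rows with no drug effect, where the term is purely a marker of non-response and the losses are 0.77 to 2.77.

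**Under equal management the error is conservative.** Correct for false positives. Equal management is not assured in a single-blind trial with discretionary changes, although nothing in the article shows that it would be unequal.

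**The full analysis plan may settle this.** The point is not an omission: the article names the covariate.

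**Conclusion.** The term is wrong as written. The mixed model conditions on a consequence of treatment, and its coefficient is neither the randomised effect nor the effect without drug changes. That conclusion needs no assumptions beyond the article's own rules.

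The size does need them: roughly 0.1 to 2.8 mmHg towards no effect when the true effect is 8 mmHg, larger when office and 24-h BP move together more closely, and about zero with no true effect and equal management. The direction is not guaranteed if management differs between arms.

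This should be fixed. It becomes a must-fix if the mixed model is the primary analysis, which the article leaves open.

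**What to change.** - Delete the term for drug changes made during follow-up from the mixed model.
- State that the drug-type term means the standardised regimen at baseline. The wording is harmless if that is what it means, and has the same fault if it covers drugs taken later.
- Keep baseline BP, and include centre as the randomisation stratum.
- State whether the mixed model is primary or supportive, and for which BP measure.
- Report drug changes by arm, building on the medication-adjustment outcome already listed under Outcome measures.
- If the effect without drug changes is of interest, define it and address it in a separate sensitivity analysis, for example by setting BP after a drug change to missing and imputing it under stated assumptions.

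The cost is an edit to one sentence and, if wanted, one sensitivity analysis. No extra data are needed and the sample size is unaffected. Trial status says recruitment had not begun at submission, so at that point the change could be made before any outcome was seen.
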